**III. Study Design**

1. Provide an overview of your study design and methods. The study design must relate to your stated aims/objectives. Details will be requested later. If your study also involves analysis of existing data, please complete Section XI, “Secondary Data Analysis of Existing Data” in the last part of this research plan. If your study ONLY involves analysis of existing data, please use the research plan template for secondary data analysis (JHSPH IRB Research Plan for Secondary Data Analysis of Existing Data/Specimens).

AIM 1: Pilot measurement tools assessing identified priority mental health conditions, functional impairment and intimate partner violence in Nyarugusu refugee camp

We have selected measurement tools that have been used in previous research on mental health and IPV and were consistent with the priority mental health and psychosocial problems affecting female survivors of IPV in Nyarugusu identified in our previous qualitative research (please see section V.B.4 and attached measures). However, because these tools have not been validated in Congolese refugees residing in Nyarugusu refugee camp, we plan to conduct a validation study prior to starting the randomized controlled trial. For the validation study we will recruit 60 women from zone 1 meeting the eligibility criteria for the trial to complete the screening and baseline assessment and participate in the intervention during the pilot period. The measurement validation and pilot intervention activities will be implemented by the research staff and intervention facilitators hired to complete the randomized controlled trial. For purposes of measurement validation, we will not conduct the post-intervention assessment with the pilot participants because there are no new measures introduced during these assessments. Thus, completing the screening and baseline assessments during the pilot phase will be sufficient for completing our objective of evaluating the validity and reliability of these measurement tools among women in Nyarugusu. Using pilot measurement validation data we will be able to assess inter-rater reliability, internal consistency, construct validity, test-retest reliability and face/content validity as follows.

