1. Provide a sample size and a justification as to how you arrived at that number. If you use screening procedures to arrive at a final sample a table may be helpful.

Pilot Study:

We have chosen to include 60 women in the measurement validation and pilot intervention phase because this sample size will allow for each pair of facilitators (5 pairs in total) to run through the entire intervention starting with 12 women each. Sixty participants is also a sufficient sample size to meet the objectives of our measurement validation activities.

Randomized Controlled Trial:

Our primary outcomes are both assessed on a continuous scale, thus we conducted a sample size calculation for the randomized controlled trial intended for two-sample mean comparisons using one of our primary outcomes of interest, psychological distress. We gathered information from previous trials measuring our primary outcome(s) of interest in similar populations to estimate the following parameters used for the sample size calculation:

$$\sigma_{time1}^{2}=0.25$$

$$\sigma_{time2}^{2}=0.36$$

$$\rho=0.333$$

$$\sigma_{change}^{2}=0.55007$$

$$m=10$$

$$\mu_{1}=1.3$$

$$\mu_{2}=0.7$$

$$N=\frac{2\left( z_{\frac{\alpha}{2}}+z_{\beta} \right)^{2}(\sigma^{2})(1+\left( m-1 \right)\rho)}{{(\mu_{1}-\mu_{2})}^{2}}=\frac{2\left( 1.96+0.842 \right)^{2}(0.55007)(1+\left( 18.269-1 \right)0.333)}{{(1.3-0.7)}^{2}}=161.97$$

In order to have 80% power to detect a treatment effect of similar magnitude as previous trials that are roughly comparable in terms of intervention and population at the 0.05 significance level, we need 162 persons per group. To account for 10% attrition, we will recruit a target sample of 180 participants per group (360 total).

Process Evaluation:

We will conduct a total of 28 qualitative interviews as part of the process evaluation. We will recruit a subset of the participants that were enrolled in the randomized controlled trial (n=10) to participate in the process evaluation. We will recruit 10 intervention facilitators, their clinical supervisor (n=1) and 7 members of local partner organization to interview regarding implementation facilitators and challenges. These new participants will not be interviewed regarding personal health information and the focus of the interviews will be on program implementation.

Total Sample Size:

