**IV. Participants**

Describe the study participants and the population from which they will be drawn. Specify the inclusion and exclusion criteria. If you plan to include children, note their ages and whether you will include children in foster care. Note if the participants are particularly vulnerable in terms of cognitive limitations, education, legal migration status, incarceration, poverty, or some combination of factors.

Congolese refugee women residing in Nyarugusu camp in northwest Tanzania reporting a past-year history of intimate partner violence and experiencing moderate to severe psychological distress will be included in this study. We will initially invite women to participate that are members of women’s groups that operate throughout the camp. Women’s groups in Nyarugusu have been organized as a mechanism to strengthen social support among women in the camp. The types of women’s groups include cooking, weaving, tailoring and microfinance. Women’s groups are formed by IRC and other agencies in the camp; however, women from the community may propose to start a women’s group to these agencies as well. Each women’s group contains approximately 11-20 women and they each elect a leader that organizes group meetings and activities throughout the camp. Members organize most women’s group activities, however IRC and other agencies do occasionally provide skills trainings to women’s groups at the women empowerment center or other venues throughout the camp. In addition to recruitment through women’s groups, we will also include women that are referred to the program so long as they meet the following eligibility criteria:

1. Inclusion criteria:
   1. 18+ years of age
   2. Female
   3. Refugee from the DRC residing in Nyarugusu refugee camp
   4. Past-year history of intimate partner violence (survivor)
   5. Experiencing moderate to severe levels of psychological distress during the past month as measured by the 25-item Hopkins Symptom Checklist and the Harvard Trauma Questionnaire (Average Score >=1.75 on either checklist, indicating close to a moderate amount of distress)
2. Exclusion criteria:

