We anticipate that this quality assurance procedure will last approximately 2-3 minutes and will not be the source of unnecessary burden or any additional risk to the participant.

Intervention Study Visits: If a participant belongs to a women’s group randomly assigned to the intervention condition, a member of the intervention team will contact her to schedule the first intervention session. The intervention facilitators are former/current International Rescue Committee counselors involved in gender-based violence programming in the camp. The facilitators received thorough training in the Nguvu intervention, which consists of two advocacy/empowerment sessions and six cognitive processing therapy sessions. The first session of the Nguvu intervention is an individual session in which a single trained facilitator meets with the participant to discuss intimate partner violence, psychological distress and to develop a safety and emergency plan. This initial session is followed by seven group sessions of 10-12 participants led by two trained facilitators. Sessions 2-7 are adapted from the Cognitive Processing Therapy (CPT) Manual previously tested among survivors of sexual and gender-based violence in eastern DRC (Bass et al., 2013). The final session (8) integrates CPT principles and revisits the safety plan developed during session 1. A summary of session content is shown in Table 1.

Table 1. Summary of Nguvu Intervention

| **Session** | **Topic** | **Description** | **Homework Activities** |
| --- | --- | --- | --- |
| 1. Empowerment/ Advocacy | Advocacy and safety plan | - Information on IPV - Discussing psychological distress - Danger assessment - Safety plan and emergency plan | Safety plan |
| 2. CPT | Intro to CPT in Nguvu | - Introducing group rules and overview of Nguvu sessions - Stuck thoughts - Explanation of thoughts and feelings - Treatment goals | Notice and explore thoughts and distress related to IPV |
| 3. CPT | ABCs | - Introduction of ABCs - Exploring stuck points - Group relaxation | Daily practice of ABCs and relaxation task |
| 4. CPT | Stuck points and thinking questions | - Changing thoughts and feelings - Thinking questions - Exploring stuck thoughts | Daily practice of ABCs and exploration of stuck thoughts; relaxation task |
| 5. CPT | Learning safety and trust | - Introduction to safety and trust - Stuck thoughts related to trust | Daily practice of ABCs, thinking questions and changing thoughts |

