The primary goal of the study is to evaluate whether levels of psychological distress, intimate partner violence and/or functional impairment differ by exposure to the experimental intervention. To assess this quantitatively we will construct multilevel mixed effects models that account for the clustered design (within women’s groups) and allow for longitudinal analysis of the changes in these outcomes (while accounting for within-person clustering). Given that this is a randomized controlled trial, we do not anticipate any pre-treatment confounding, but will evaluate the similarity between groups in terms of important covariates at baseline. We are also including measures of hypothesized mediators and moderators of intervention efficacy that will be analyzed as our secondary analyses.

1. Describe whether you are collecting or storing personal identifiers, and if yes, why you need them, and when and how you plan to dispose of them. Signatures on consent forms are considered to be identifiers.

There are two points in the program at which we collect and store personal identifiers. The first is after the screening at which time we ask for the participant’s contact information to allow for communication with the participant throughout the follow-up period, as well as a signature (or thumbprint) on the consent forms. Immediately following the interview, this information will be placed in a double-lock safe in the research team office. The in-country project coordinator will input this information into a password-protected file that connects the participants alphanumeric ID with their name and contact information. This is the only place that this information will be connected. Afterwards, the physical contact sheet will be shredded. The consent forms will also contain personal identifiers. These consent forms will also be kept in the double-lock safe in the research team office.

6. Answer the following **if they are relevant to your study design**:

a. If the study has different arms, explain the process for assigning participants (intervention/control, case/control), including the sequence and timing of the assignment.

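### The stated model clusters by women's group and woman only, yet Nguvu is delivered in shared therapy groups by facilitator pairs in one arm; where these cut across women's groups, the confidence intervals can be too narrow.

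*Protocol*

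**What the plan says.** The data analysis plan in protocol section V.C names two levels of clustering for the outcome models: "multilevel mixed effects models that account for the clustered design (within women’s groups" and, for the repeated measurements, "while accounting for within-person clustering". No other level is named.

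Delivery is described elsewhere:

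- **Therapy groups.** Section V.C, Intervention Study Visits: after one individual session come "seven group sessions of 10-12 participants led by two trained facilitators". Control women have the same assessments but none of these sessions.
- **Facilitator pairs.** Section III, sample size for the pilot, refers to "each pair of facilitators (5 pairs in total) to run through the entire intervention". The figure is given for the pilot. However, Aim 1 in section III says the pilot activities are "implemented by the research staff and intervention facilitators hired to complete the randomized controlled trial", and the process-evaluation list in section IV counts ten facilitators in the trial, which again makes five pairs.
- **Women's groups.** Section IV: "Each women’s group contains approximately 11-20 women". That is membership before eligibility screening. Sections IV and V.A also admit referred women, including women who belong to no women's group.

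The protocol does not say how enrolled women are placed into therapy groups, or whether those groups follow women's groups or mix them. It gives no ICC for therapy group or for facilitator pair.

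**The concern.** Women who share seven sessions and the same two facilitators may have correlated outcomes. Such correlation adds variance to the intervention-arm mean and has no counterpart among controls. A women's-group random effect common to both arms picks up this variance only to the extent that therapy groups and pairs line up with women's groups.

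Where they do not, the variance of the treatment difference is understated for both primary outcomes (distress and intimate partner violence) and for functional impairment. The interval is then too short, the type I error is above the stated 0.05, and part of what is reported as an intervention effect may reflect one good or poor group or pair.

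The layout makes crossing likely. To fill a therapy group of 10 from one women's group, between 10/20 = 50% and 10/11 = 91% of its members would have to be eligible and consent. Referred women must in any case be seated with others. Even if therapy groups followed women's groups exactly, each pair would lead about three of them.

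**Working it through.** **Inputs from the protocol (section III, sample size).** ICC 0.333; variance of change 0.55007; difference 1.3 − 0.7 = 0.6; z-values 1.96 and 0.842; cluster size m listed as 10 but entered in the formula as 18.269; 162 per arm, 180 after 10% attrition.

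**The plan's own figure.** The design effect with m = 18.269 is 1 + 17.269 × 0.333 = 6.751. Then N = 2 × 2.802² × 0.55007 × 6.751 / 0.36 = 161.97, which reproduces. With the listed m = 10 the design effect is 3.997 and N is 95.9, which does not. That discrepancy is a separate matter; both values of m are carried below.

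**Layout of delivery.** 180 women in groups of 10-12 make 180/12 = 15 to 180/10 = 18 therapy groups. Five pairs have 180/5 = 36 women each, or 3 to 3.6 therapy groups. Women's groups per arm number 180/18.269 ≈ 10 to 180/10 = 18, so a pair normally spans several.

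**Assumptions, because the protocol gives no figure.** Therapy-group ICC ρt of 0.05-0.10; pair ICC ρf of 0-0.05; pairs fixed through the trial.

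**Closed form, therapy groups cutting across women's groups.** In squared-SD units with 162 analysed per arm:

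- Variance of the difference under the stated model = 2 × DE / 162.
- Omitted variance in the intervention arm = ρt / 14.7 + ρf / 5, where 14.7 = 162/11.

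At DE 6.751 the model variance is 0.0833:

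| ρt | ρf | Omitted variance | Variance ratio | True SE / model SE | Type I error (normal approx.) | Power if SE is correct |
|---|---|---|---|---|---|---|
| 0.05 | 0 | 0.0034 | 1.04 | 1.02 | 5.5% | 78% |
| 0.05 | 0.02 | 0.0074 | 1.09 | 1.04 | 6.0% | 77% |
| 0.10 | 0.05 | 0.0168 | 1.20 | 1.10 | 7.4% | 73% |

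The base matters. At ICC 0.333 with m = 10 the model variance is 2 × 3.997/162 = 0.0493, and the SE ratio runs from 1.03 to 1.16 over the same three rows. At an assumed women's-group ICC of 0.05 with m = 10 it is 2 × 1.45/162 = 0.0179, and the SE ratio runs from 1.09 to 1.39.

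**Simulation.** Under the null, with 180 per arm and 4,000 runs per cell, the analysis was the balanced equivalent of a women's-group random-intercept model. Layouts were 18 women's groups of 10 and 10 of 18; women's-group ICCs were 0.05 and 0.333. The Monte Carlo standard error at 5% is √(0.05 × 0.95/4000) = 0.3 percentage points. With no therapy-group or pair effect, rejection was 4.2-5.1%.

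| Therapy groups | Pair effect | Type I error, nominal 5% |
|---|---|---|
| Coincide with women's groups | none | 4.5-5.6% |
| Coincide | ICC 0.02-0.05 | 4.5-8.9% |
| Cut across | none | 5.8-8.2% |
| Cut across | ICC 0.02-0.05 | 6.5-14.7% |

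At women's-group ICC 0.333 with cutting across, the range over both layouts is 5.8-8.8%. The largest values are 7.7% with groups of 18 and 8.8% with groups of 10. The 14.7% arises at ICC 0.05 with groups of 10.

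**The case against.** The form asks for a brief analysis plan. The plan correctly names the randomised cluster and the repeated measures, does not rule out further terms, and an SAP not shown may add them. No section says that therapy groups mix women's groups. The planning cluster sizes of 10 and 18.269 are about as large as a therapy group or larger, so forming therapy groups within women's groups is feasible on those figures. In that case the women's-group effect absorbs the therapy-group variance, and a separate therapy-group term would be aliased with it in that arm. Five pairs cannot give a well-estimated pair variance, and treating the facilitators as part of the tested package is a defensible choice of inference.

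Much of this stands, and it limits the point. A reader might infer that the intervals are too narrow whatever the layout. The documents do not support that: with coinciding groups and no pair effect, simulated type I error is 4.5-5.6%. A reader might also infer that error rates of 9-14% are to be expected. Rates much above 9% need a women's-group ICC well below the stated 0.333, and the protocol gives no such value. Nor does it say that scheduling already produces therapy-group or pair identifiers.

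Brevity does not remove the point. The plan states which clustering the model handles, and that list does not match the delivery described in the same protocol.

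**Conclusion.** The concern holds conditionally. The stated clustering leaves out a source of correlation that exists in one arm only. Therapy groups will probably mix women's groups and pairs almost certainly will, but the first is an inference from group sizes, screening and referral, and the second assumes the five pilot pairs carry into the trial.

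Where they mix, intervals can be too narrow. At the protocol's own inputs the effect is modest: the true standard error is about 2-10% above the model's, type I error is about 6%, and the worst simulated case at that ICC is about 9%. It becomes serious, up to about 14-15%, only if the women's-group ICC is small. All therapy-group and pair ICCs are assumed. If therapy groups are formed within women's groups and pairs do not differ, the stated model is adequate.

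**What to change.** In the data analysis plan of section V.C:

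1. State how therapy groups are formed relative to women's groups, including where referred women are placed.
2. Record a therapy-group identifier and a facilitator-pair identifier for every intervention participant. If they are not recorded during the trial, the correction may not be recoverable later.
3. Where therapy groups cut across women's groups, add a therapy-group random effect in the intervention arm only (a partially nested model), alongside the women's-group effect in both arms. Where the two coincide, this term is not needed.
4. Report a sensitivity analysis for facilitator pair. Keep pair out of the primary model, because five pairs are too few to estimate its variance well.

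The cost is a few sentences, two identifiers to record and somewhat wider intervals. At the protocol's inputs, and under the assumed ICCs, power for the stated effect would be about 73-78% rather than 80%.

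### The trial is sized on the variance of change and the model is described in terms of changes, with no stated adjustment for the baseline score; the primary model should be named, and a baseline-adjusted form is usually more precise

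*Protocol*

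**What the plan says.** Each woman is assessed at baseline (week 1) and once after the intervention (week 10).

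**Section III, sample size for the randomized trial.** The inputs for psychological distress include "\sigma_{time1}^{2}=0.25", "\sigma_{time2}^{2}=0.36" and "\sigma_{change}^{2}=0.55007". A correlation of 0.333 is listed directly after the two time-point variances, but the formula uses it as the intracluster correlation. The result is stated as "In order to have 80% power to detect a treatment effect of similar magnitude as previous trials" and "at the 0.05 significance level, we need 162 persons per group", followed by "To account for 10% attrition, we will recruit a target sample of 180 participants per group (360 total").

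**Section V.C, data analysis plan.** The aim is to see whether levels of the outcomes differ by arm. The models are to account for women's groups and to "allow for longitudinal analysis of the changes in these outcomes (while accounting for within-person clustering"). On baseline it says "Given that this is a randomized controlled trial, we do not anticipate any pre-treatment confounding" and adds that the similarity of the arms on important covariates will be examined. The fixed effects are not listed, and adjustment for the baseline value of the outcome is not mentioned.

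**The concern.** Taken together, the two sections point to a comparison of mean change between arms. In a mixed model with two time points, complete data and a separate baseline mean for each arm, the arm-by-time coefficient equals the difference in mean change.

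That is an inefficient use of the baseline unless it correlates strongly with follow-up. The Protocol's own figures imply that it does not: change is put at 0.55007 and the follow-up score alone at 0.36, so subtracting the baseline adds noise. If the fitted model is a change comparison, the intervals for distress are likely to be wider than they need be.

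Chance baseline differences also matter when few clusters are randomised. A similarity check describes them without correcting them. A change score removes the whole baseline difference, which is too much when the regression slope of follow-up on baseline is below 1.

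**Working it through.** **Inputs (Section III, distress).** Baseline variance 0.25 (SD 0.5), follow-up variance 0.36 (SD 0.6), variance of change 0.55007, correlation 0.333 used as the intracluster correlation, cluster size 10 as listed and 18.269 as used, difference 1.3 − 0.7 = 0.6, z-values 1.96 and 0.842.

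**1. Reproduce the stated size.** The design effect is 1 + 17.269 × 0.333 = 6.75. Then N = 2 × 2.802² × 0.55007 × 6.75 / 0.6² = 161.97 per group, and 162 / 0.9 = 180. Both stated figures reproduce, but only with cluster size 18.269. The listed value of 10 gives 95.9, which is a separate discrepancy.

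**2. What 0.55007 implies.** With r the correlation between baseline and follow-up:

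Var(change) = 0.25 + 0.36 − 2r(0.5)(0.6) = 0.61 − 0.6r.

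- Setting this to 0.55007 gives r = (0.61 − 0.55007) / 0.6 = 0.0999.
- If 0.333 had been meant as r, the variance would be 0.61 − 0.6 × 0.333 = 0.4102.
- 0.61 − 2 × 0.333 × 0.5 × 0.6 × 0.3 = 0.55006, so the product of the two SDs (0.3) may have been applied twice. That is a guess at the origin. The Protocol nowhere states r = 0.10.

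**3. Individual-level comparison.** The variance of the follow-up score adjusted for baseline is 0.36(1 − r²).

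| r | Change | Follow-up alone | Baseline-adjusted | Reduction, adjusted against change |
|---|---|---|---|---|
| 0.10 | 0.5501 | 0.36 | 0.3564 | 35.2% |
| 0.333 | 0.4102 | 0.36 | 0.3201 | 22.0% |
| 0.5 | 0.3100 | 0.36 | 0.2700 | 12.9% |
| 0.7 | 0.1900 | 0.36 | 0.1836 | 3.4% |
| 0.833 | 0.1100 | 0.36 | 0.1100 | 0% |

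At r = 0.10, follow-up alone is already 34.6% below 0.55007. Adjustment adds only about 0.7 percentage points.

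**4. Cluster-level comparison.** At cluster size 18.269 and intracluster correlation 0.333, the between-cluster share of the variance of an arm mean is 0.333 × 18.269 / 6.75 = 0.90. The cluster-level correlation between baseline and follow-up therefore governs the gain, and the Protocol gives none. I simulated 10 clusters per arm (180 / 18.269 = 9.9) of 18 women, with intracluster correlation 0.333 at both times and adjustment on cluster means. The variance of the adjusted arm difference relative to the change-score difference was:

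| Cluster-level correlation | Ratio |
|---|---|
| 0.1 | about 0.69 |
| 0.333 | about 0.82 |
| 0.5 | about 0.90 |
| 0.7 | about 1.00 |
| 0.9 | up to about 1.07 |

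The ratio above 1 is the price of estimating a slope from 20 clusters when the change score is already close to optimal.

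**5. Chance imbalance at baseline.** Borrowing 0.333 as the intracluster correlation of the baseline score, the standard error of the baseline difference is √(2 × 6.75 / 180) = 0.27 SD. With the listed cluster size of 10 there are 18 clusters per arm and the design effect is 1 + 9 × 0.333 = 4.00, giving √(2 × 4.00 / 180) = 0.21 SD. The regression slope of follow-up on baseline is r × 0.6 / 0.5 = 1.2r, that is 0.12 at r = 0.10 and 0.40 at r = 0.333, against the slope of 1 that a change score imposes.

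**The case against.** **The model is not fixed as change from baseline.** A reader might infer that the Protocol commits to a change-score analysis. It does not. The goal is worded in terms of levels, the fixed effects are not given, and a longitudinal model with baseline means constrained equal fits the same sentence and is about as efficient as baseline adjustment. A brief plan may leave these terms to an SAP that is not at hand. This stands: the change-score reading is the natural one, supported by the sizing, but it is an inference.

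**About a third, at no cost.** A reader might take 35% as the expected gain. It rests on r = 0.10, back-solved from a figure that may be an arithmetic slip, and nearly all of it comes from not subtracting baseline. It also assumes the same design effect for both analyses. With about ten clusters per arm the gain runs from about 30% to none, with a possible small loss. This stands.

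**Both primary outcomes.** The variances are for distress only. The Protocol does not support a figure for intimate partner violence or functional impairment.

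**Imbalance ignored.** The sentence about confounding goes on to promise a similarity check, and a change analysis also removes baseline differences. It would be wrong to say that the Protocol ignores baseline, or that only adjustment handles imbalance. What remains is that a check corrects nothing and a change score over-corrects at low r.

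**Different targets.** Women's groups are randomised before recruitment (Section V.C.6.a). If enrolment then differs by arm, adjusted and change analyses can estimate different things. This is a genuine downside, and also a reason to name the estimator in advance.

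**Sizing on change is conservative.** At the same design effect, 0.3564 in place of 0.55007 would give 104.9 per group instead of 162, or 93.6% power at 162. With r unknown and the cluster size inconsistent, this does not justify a smaller trial.

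**Conclusion.** The point holds in a limited form. The trial is sized on a variance of change that exceeds its own follow-up variance. The analysis is described in terms of changes, and no adjustment for the baseline score is stated. If the model is an arm-by-time model with free baseline means, it is a change-score comparison and will usually be less precise than one using the same data with baseline adjusted for or constrained equal.

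For distress, the individual-level reduction is 22% to 35% for r between 0.333 and 0.10, and smaller if r is higher. Allowing for clustering, it is about 30% at a cluster-level correlation of 0.1, nil near 0.7, and a loss of up to about 7% near 0.9. The clustered figures assume about ten clusters per arm and an intracluster correlation of 0.333. The listed cluster size of 10 would give 18 clusters per arm.

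The Protocol does not show that the trial is underpowered for this reason, that a third of the variance is certain to be saved, or that the gain carries over to the other outcomes.

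**What to change.** **Section V.C, data analysis plan.** Name one of these as the primary model:

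- the follow-up score on arm, adjusted for the woman's own baseline score, with a random intercept for women's group. The group mean of baseline can be added only where a group is defined, because Section V.A.1 also admits referred women who belong to no group; or
- a longitudinal mixed model with baseline means constrained equal across arms, with the same clustering terms.

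**Section III, sample size.** State r separately from the intracluster correlation, and make the variance agree with it: 0.61 − 0.6r if change is analysed, or 0.36(1 − r²) if baseline-adjusted. Show the result over a range of r and reconcile the two cluster sizes at the same time.

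**Cost.** Wording and a recalculation; both scores are already collected. The downsides are the possible small loss when cluster-level correlation is very high, and the difference in what is estimated if recruitment after randomisation differs by arm. The plan should acknowledge both.
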